### Hypotheses

The principal hypothesis is as follows: Pain perceived during the collection of an arterial blood sample in the ED is lower when it is performed using positive therapeutic communication compared to neutral or nocebo communication.

The secondary hypotheses are as follows:

Discomfort perceived during the collection of an arterial blood sample in the ED is lower when the procedure is conducted using positive therapeutic communication compared to neutral or nocebo communication.Anxiety perceived during the collection of an arterial blood sample in the ED is lower when the procedure is conducted using positive therapeutic communication compared to neutral or nocebo communication.

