### Outcomes

The primary outcome is pain: self-evaluation of the maximum pain felt by the patient during the collection of an arterial blood sample on the Verbal Rating Scale (VRS: 0=no pain to 10=the worst imaginable pain) just before the beginning of the procedure and during the procedure (question asked during the 3 minutes after the procedure) [14,31,32].

The secondary outcomes are as follows:

Comfort: self-evaluation of patient comfort using a simple comfort VRS (0=no comfort to 10=the most comfort imaginable) just before the beginning of the procedure and 3 minutes after the procedure [33]Anxiety: self-evaluation of patient anxiety using a simple anxiety VRS (0=no anxiety to 10=the worst anxiety imaginable) just before the beginning of the procedure and 3 minutes after the procedure [34]Puncture failure: success of the first arterial puncture assessed by the accredited evaluator at the end of the procedure using the number of puncture points visible on the patient’s skin (possible response: 1 puncture visible, yes/no)Global satisfaction with the communication strategy used: evaluation by the patient at the end of the procedure using a numeric scale of 0-10 (0=extremely dissatisfied to 10=extremely satisfied)

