### Statistical Analysis

#### Sample Size Calculation

With a significance level of .05, a power of 0.9, a difference in pain on the VRS of 1.5 (generally accepted as clinically significant) with an expected SD of 2.5 [35], and an attrition of 20% on the basis of a group-independent *t* test (a specific case of linear mixed effects models [LMMs]), we must include 83 patients in each group to show the efficacy of the intervention on pain by applying the Bonferroni correction (ie, a total of 249 patients).

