#### Statistical Analysis Plan

First, descriptive statistics (frequencies and percentages for categorical data; means, SDs, medians, and IQRs for quantitative data) will be run for each measure of time for each group and the overall study sample. In addition, an analysis of nonresponses and patient dropouts will be conducted. Second, bivariate associations will be calculated to compare the groups at baseline (Pearson chi-square test, Fisher exact test, *t* test, and the Mann-Whitney test according to the distribution of variables). Third, to test the impact of the intervention on the different outcomes (hypotheses 1, 2, and 3), LMMs with patients, groups and physicians as a random effect will be performed to analyze changes over time. The participation of approximately 25 physicians is foreseen in this study. The models will be tested on all available data.

The effects of time, groups, and their interaction will be tested by controlling for sociodemographic characteristics and variables linked to health status. An intention-to-treat (ITT) analysis, per protocol (PP) and based on the analysis of communications (ie, the respect of the quality of the defined communication according to the protocol; see the next section), will be conducted. The Pearson chi-square test comparing the allocation defined in the protocol and the allocation following the analysis of communications will be performed. If necessary, a generalized LMM will also be used to explore the differences between the available measured variables (physicians having performed the ABG procedure, pain, etc). Statistical analysis will be performed on available data, and no imputation of missing data will be conducted. Given that our study will be conducted on a 1-to-1 basis with a member of the research team and on the basis of previous experience, we expect that the number of missing values will be low. Statistical analyses will be performed using the R (R Core Team and the R Foundation for Statistical Computing) and STATA version 12 (StataCorp); the level of significance will be set at *P*=.05.

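### Primary test does not match the sizing or the hypothesis: a time-by-group interaction without adjustment for pre-procedure pain has less power than the sizing test if the two pain ratings correlate weakly

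*Protocol article*

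**What the plan says.** Four sections of the protocol article bear on this.

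- **Hypotheses.** The principal hypothesis is about a level of pain at one time: "Pain perceived during the collection of an arterial blood sample in the ED is lower" with positive communication than with the other two scripts.
- **Outcomes.** Pain is rated twice on the 0-10 scale: "just before the beginning of the procedure and during the procedure (question asked during the 3 minutes after the procedure".
- **Sample Size Calculation.** The inputs are "With a significance level of .05, a power of 0.9, a difference in pain on the VRS of 1.5", a single SD of 2.5 and 20% attrition, with a Bonferroni correction. The test is a t test for independent groups, justified as "a specific case of linear mixed effects models". No pre-post correlation is given. The section does not say whether 2.5 is the SD of a single rating or of a change.
- **Statistical Analysis Plan.** Mixed models are used to study change over time for all three hypotheses: "The effects of time, groups, and their interaction will be tested by controlling for sociodemographic characteristics and variables linked to health status". Pre-procedure pain is not named among the adjustment variables, and the section does not say which of the three effects decides the hypothesis.

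**The concern.** The t test is indeed a special case of a mixed model, but of one fitted to a single rating per patient. Once both ratings enter as outcomes, the time-by-group interaction is the between-arm difference in change. Its variance depends on how strongly the two ratings correlate, and the sizing does not take this into account.

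In this setting the correlation could be low. Pain before the procedure comes from the presenting condition, and pain during it comes largely from the needle. Subtracting a weakly related baseline adds noise to the comparison of interest. The stated 90% power would then not describe the test that is run, although the ratings needed for a more precise analysis are already collected.

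**Working it through.** **Inputs from the protocol.** Difference 1.5, SD 2.5, family alpha .05, power 0.9, attrition 20%, 83 per arm.

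**Assumptions.** Tests are two-sided. The Bonferroni divisor is 2, because the principal hypothesis compares positive communication with two other arms, so alpha is .025. SD 2.5 belongs to a single rating. SDs before and during the procedure are equal. r is not given, so a range is shown. Clustering by physician is ignored throughout.

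**Step 1: the plan's own figure.** n = 2 × (2.241 + 1.282)² × (2.5/1.5)² = 68.95, so 69 per arm. 69 × 1.2 = 82.8, so 83. The stated size is reproduced, with attrition added as a 20% mark-up. If 20% of 83 are really lost, 83 × 0.8 = 66.4 complete, and the t test then has power 0.88 (noncentral t). About two points of the gap from 0.90 therefore come from the attrition arithmetic and not from the choice of test.

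**Step 2: formulas.**
- Interaction (change score): effect 1.5, SD = 2.5 × √(2(1−r)).
- Baseline-adjusted procedural pain: effect 1.5, residual SD = 2.5 × √(1−r²).
- Group effect averaged over both times: the arms cannot differ systematically before the script starts, so the effect is (0 + 1.5)/2 = 0.75, with SD = 2.5 × √((1+r)/2).

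**Step 3: power with 66.4 per arm, two-sided alpha .025.**

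| r (assumed) | SD of change | Interaction | t test of procedural pain | Baseline-adjusted | Group effect averaged over time |
|---|---|---|---|---|---|
| 0 | 3.54 | 0.57 | 0.88 | 0.88 | 0.57 |
| 0.3 | 2.96 | 0.74 | 0.88 | 0.91 | 0.45 |
| 0.5 | 2.50 | 0.88 | 0.88 | 0.96 | 0.40 |
| 0.6 | 2.24 | 0.94 | 0.88 | 0.98 | 0.37 |

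**Step 4: ordering.** 2(1−r) − (1−r²) = (1−r)² ≥ 0, and 1−r² ≤ 1. At every r, the adjusted analysis is therefore at least as precise as both the change score and the plain t test, apart from one degree of freedom, which is negligible at this size.

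**Step 5: unequal SDs.** The variance of change is SD_pre² + SD_post² − 2r × SD_pre × SD_post. It equals SD_post² at r = SD_pre/(2 × SD_post). This break-even is 0.5 for equal SDs, 0.4 if SD_pre is 80% of SD_post, and 0.6 if it is 120%.

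**Step 6: other readings of the sizing.** With 69 per arm, the same calculation gives 0.76 for the interaction at r = 0.3, against 0.89 for the t test and 0.92 with adjustment. The ordering does not depend on alpha or n.

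**The case against.** The strongest reply is that the loss of power is conditional and could be nil.

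- The sizing section names no time point for the 1.5 and does not say what 2.5 is the SD of. If it is the SD of a change, sizing and interaction agree. This stands as a possibility. The section speaks of a difference in pain, however, so a single rating is the more natural reading, and adjustment would be at least as precise either way.
- A reader might infer that the trial is underpowered. The documents do not support that. They give neither r nor the pre-procedure SD, and above the break-even the interaction beats the sizing test (0.94 against 0.88 at r = 0.6). With an assumed SD_pre of 1.5, break-even falls to r = 0.3, and interaction power is 0.76 even at r = 0.
- A reader might also infer that the primary result will rest on a group effect cut to half. That holds only if group is tested as an average over both times, which the article does not say. With the procedural rating as the reference time, the group coefficient is the arm contrast at that time.
- Coding and choice of contrast can be left to a fuller analysis plan. This stands in part. But the article itself fixes a model of change over time, lists the effects to be tested, and names adjustment variables that do not include pre-procedure pain.
- The interaction is a valid, unbiased test under randomisation. This stands in full.

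**Conclusion.** The point holds as one of efficiency and of matching the test to the hypothesis, not of bias. The sizing test and the planned interaction have equal power only at the break-even correlation, which is 0.5 if 2.5 is the SD of a single rating and the two SDs are equal. Below it the interaction loses power, to 0.74 at an assumed r of 0.3 and 0.57 at r = 0, against 0.88 for the t test. Above it the interaction gains. How far the trial is affected cannot be known from the protocol. The case for adjustment does not depend on r, because the baseline-adjusted contrast is never materially less precise than either alternative. The point merits a change to the plan, with moderate confidence that the loss would be material and high confidence that the change is an improvement.

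**What to change.** Name the primary analysis: the arm contrasts in procedural pain (positive against neutral, positive against nocebo), with pre-procedure pain as a covariate and the random intercept for physician kept. A two-time mixed model with pre-procedure means constrained equal across arms, reporting the contrasts at the procedural time, serves the same purpose. State that neither the group effect averaged over time nor the unconstrained interaction is the test of the hypothesis. Say in the sample size section which rating the SD of 2.5 describes. The same model can be used for comfort and anxiety, which are also rated before the procedure; the power figures above were worked out for pain only.

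The cost is wording, settled before unblinding. No extra patients, visits or data are needed.

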#### Analyses of Communications

All communications will be recorded. We will listen to 30 communications at a time to evaluate the quality of each communication and to ensure that the communication corresponds to the defined study arm defined at the time of randomization. This evaluation will be performed until less than 10% of incorrect rankings are obtained. A physician external to patient management will reassign the patient groups based on a list of preselected keywords. This same physician will then (re)classify the patients into 1 of the following 3 arms: therapeutic positive communication, nocebo, or neutral.

The classification will be performed with the help of a list of 10 keywords provided to the external physician. Each list of 10 keywords will be associated with 1 of the 3 arms and will correspond to standardized phrases related to each arm. Thus, if the external physician finds 1 keyword associated with the nocebo arm, the patient will then be reclassified into the nocebo arm; if the external physician finds 1 keyword associated with the therapeutic positive communication arm but without any keywords associated with the nocebo arm, the patient will be classified into the therapeutic positive communication arm. If the physician does not find any keywords associated with these 2 arms, the patient will be classified into the neutral arm.

This classification will be conducted in parallel by 2 persons for the first 30 patients to evaluate the interrater reliability using Cohen κ. If κ>0.90, only 1 coder will continue to code the audio recordings. If not, 2 coders will continue to evaluate the communications; in the case of disagreement, a third coder will make the final decision.

The keywords associated with the nocebo group are as follows:

PainColdPrickDo not panic.Are you in pain? I am going to prick.This is going to sting.Do not move, it won’t be long.Do not be frightened.How do you feel?

The keywords associated with the therapeutic positive communication group are as follows:

Be reassured.Are you comfortable?Are you relieved?I am going to place the drip.Have confidence.Take it easy.It will be fast.Do you feel well?

These lists are likely to be adapted based on the audio recordings.

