### Strengths and Limitations

The main strengths of the study are its originality, the ease of implementation, and the rigorous methodological design, the last being based on a previously published study [15].

However, this study also has some limitations. First, the received communication policy may be different from the one intended to be used. To limit this bias and avoid any contamination of the arms due to inappropriate communication, all procedures will be recorded and replayed to verify whether the attributed group and the received communication scheme correspond. Second, this is a single-center study. The experience of the physicians performing the ABG procedure, although similar, is quite limited, which could interfere with the communication, as these inexperienced physicians may focus more on the correct technical execution of the ABG procedure than on the communication. In addition, nonverbal communication during the interview will not be studied. Third, other uncontrolled confusing factors could affect the results (eg, a long wait in the waiting room for the patient and overloaded service for the doctor), but we hypothesize that these factors may be similar in each group due to randomization and will thus limit the potential bias.

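### The Pearson chi-square test planned for allocated versus received communication tests association, not agreement, so its P value does not show whether the scripts were delivered as allocated

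*Protocol article*

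**What the plan says.** The Statistical Analysis Plan section names one test of allocated against received communication: "The Pearson chi-square test comparing the allocation defined in the protocol and the allocation following the analysis of communications will be performed". It gives no rule for reading the result beyond the general statement that "the level of significance will be set at *P*=.05".

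The received category comes from the audio coding described under Analyses of Communications, which places each patient in one of the same three arms used at randomization. The purpose is given under Strengths and Limitations: "all procedures will be recorded and replayed to verify whether the attributed group and the received communication scheme correspond".

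Three other elements bear on fidelity:

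- Analyses of Communications has recordings heard 30 at a time and adds: "This evaluation will be performed until less than 10% of incorrect rankings are obtained".
- Data Monitoring has an independent person check the first 30 patients, with control visits if more than 10% of communications differ from the allocation.
- The Statistical Analysis Plan adds per-protocol and as-communicated analyses to the intention-to-treat analysis.

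Cohen's kappa is planned only for reliability between coders, not for allocated against received communication.

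**The concern.** Allocated arm and coded arm are two classifications of the same patients on the same scale. The useful question is how often they match, and in which arm they fail to. Pearson's test asks instead whether the coded arm is unrelated to the allocated arm. Rejecting that shows only that the allocation had some influence on what was said. It does not distinguish good delivery from mediocre delivery, or correct delivery from systematic delivery of the wrong script.

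Delivery of the script is the intervention here. About 25 physicians without in-depth training in positive communication deliver all three arms, and the article lists non-delivery as its first limitation. Readers will want the delivery rate in each arm when they interpret the result, above all a null one. The named test does not supply it.

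**Working it through.** **Inputs.** From Sample Size Calculation: "With a significance level of .05, a power of 0.9, a difference in pain on the VRS of 1.5", "with an expected SD of 2.5", 20% attrition and a Bonferroni correction, leading to "we must include 83 patients in each group to show the efficacy of the intervention on pain". The delivery rates below are illustrations; the article gives none.

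**The plan's own figure.** Assume two-sided testing and Bonferroni for two comparisons (neither is stated). Then n = 2(z₀.₉₈₇₅ + z₀.₉₀)²(SD/Δ)² = 2(2.241 + 1.282)²(2.5/1.5)² ≈ 69, and 69 × 1.2 = 82.8, so 83. The figure is reproduced on that reading. It is used here only for the table margins: 83 per arm, N = 249, or about 66 per arm after attrition (83 × 0.8 = 66.4).

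**Formula.** Let a be the proportion delivered correctly, with errors split evenly over the other two arms.

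- Chance agreement is 1/3, so kappa = (a − 1/3)/(2/3).
- Each row of the table is (a, (1−a)/2, (1−a)/2) in some order, and every column margin is 1/3. So chi-square = 3N[(a − 1/3)² + 2((1−a)/2 − 1/3)²] = 4.5N(a − 1/3)² = 2N·kappa², on 4 df.

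The statistic depends on kappa squared, so the direction is lost.

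**Results, N = 249.**

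| Delivery | Chi-square | P | Kappa |
|---|---|---|---|
| 100% correct | 2 × 249 × 1² = 498 | 2×10⁻¹⁰⁶ | 1.00 |
| 60% correct, even errors | 2 × 249 × 0.40² = 79.7 | 2×10⁻¹⁶ | 0.40 |
| 50% correct, even errors | 2 × 249 × 0.25² = 31.1 | 3×10⁻⁶ | 0.25 |
| 0% correct, arms swapped cyclically | 498 | 2×10⁻¹⁰⁶ | −0.50 |

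The swap lies outside the even-error formula. Its table has one cell of 83 in each row and column, as under perfect delivery, so the statistic is the same.

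**Robustness of the 50% case.**

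- Whole patients (41/21/21 in each arm): chi-square 28.9, P = 8×10⁻⁶, agreement 123/249 = 49.4%, kappa 0.24.
- 66 per arm: chi-square 24.8, P = 5×10⁻⁵.
- A numerical search over error patterns at 50% overall agreement with 83 per arm found the even split to give the smallest chi-square, so the illustration is conservative.
- Errors drifting to nocebo (rows 21/0/62, 0/21/62, 0/0/83): agreement 125/249 = 50.2%, chi-square 88.3, P = 3×10⁻¹⁸, kappa again 0.25. By arm, agreement is 21/83 = 25%, 25% and 100%. This is why figures per arm are needed beside kappa.

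**Limits of the illustration.** With even errors, significance at 0.05 needs 4.5 × 249 × (a − 1/3)² > 9.49, that is |a − 1/3| > 0.092. Delivery between about 24% and 43% would therefore not be significant. The figures also assume that all recordings are classified: in one batch of 30 at 50% correct, chi-square is 4.2 and P = 0.38.

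**What agreement measures show.** With 123/249 correct: 49.4% (95% CI about 43% to 56%), kappa 0.24. With 225/249 correct (75/4/4 in each arm): 90.4% (about 87% to 94%), kappa 0.86. The chi-square P values are 8×10⁻⁶ and 1×10⁻⁷⁷, both far below 0.05.

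**The case against.** The strongest reply is that the test does little harm. It is an ancillary line with no decision attached. The operative fidelity criterion is already a proportion of mismatches with a 10% limit, and an independent monitor applies the same limit to the first 30 patients. Delivery at 50% would plainly fail that check. The per-protocol and as-communicated analyses help to separate no effect from no delivery, and percent agreement can be read from the cross-table behind the test. All of this stands, and it limits the weight of the point.

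It does not rescue the test. The 10% limits are conduct checks on batches or on the first 30 patients, not an estimate over the whole sample by arm. Two wrong of 30, the most that falls under 10%, has an exact 95% interval of 0.8% to 22.1%. Nor is this only reporting detail left to an unseen plan: the article names a method, and the method does not answer its stated question.

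Two stronger readings are tempting, and the documents do not support them:

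- A reader might infer that a null primary result could not be told apart from non-delivery, or that the test would look reassuring whatever the fidelity. The other checks and analyses bear on non-delivery, near-chance delivery would not be significant, and the article does not say how the P value will be read.
- A reader might infer from the word *until* that listening stops after one good batch and later patients stay unclassified. The same section says that one or two coders continue to code the recordings after the first 30, and Strengths and Limitations has every procedure replayed. This is a wording ambiguity, not a plan to leave patients out.

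**Conclusion.** The point holds as a mismatch between method and question, and the plan should be changed. At the planned size, half-correct delivery with even errors gives P of about 3×10⁻⁶ with kappa 0.25, and perfect and fully swapped delivery give the same chi-square of 498. The P value therefore does not show whether the scripts were delivered as allocated.

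This rests on three equal arms of 83, all recordings classified, and delivery rates chosen for illustration. The consequence is confined to what the trial can say about fidelity. The intention-to-treat comparison, the sample size and the outcomes are unaffected.

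**What to change.** In the Statistical Analysis Plan, replace the sentence on the chi-square test with: the 3×3 table of allocated by received communication; percent agreement overall and per arm, each with a 95% CI; and Cohen's kappa with a 95% CI over all classified patients. Read the agreement against the protocol's own limit of 10% mismatch. At 90% agreement, the approximate half-width of the CI would be 1.96√(0.9 × 0.1/249) = 3.7 percentage points overall and 1.96√(0.9 × 0.1/83) = 6.5 points per arm.

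As a clarification, reconcile the batch sentence in Analyses of Communications with Strengths and Limitations by stating that all recordings are classified and that the 10% limit serves only as a monitoring trigger.

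The cost is one replaced sentence and one clarified sentence. No new data are needed: kappa is already planned for the coders, and classification of all recordings is already implied by the as-communicated analysis.

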### Case Report Form

The following data will be collected and included in dedicated CRFs. The paper CRF will contain a first part with the date of the screening, the name of the medical officer who will perform the screening, the inclusion and exclusion criteria, whether the patient has been informed orally, and whether they have provided oral consent. The medical officer will confirm whether the inclusion and exclusion criteria have been met and, if so, indicate the number of the envelope containing the random allocation to 1 of the 3 study arms; this number will be the patient's ID in the study.

Once the patient is included in the study, the assessor will fill in the second part of the paper CRF before the ABG procedure: the name of the assessor, educational level, native language (French/Swiss German/German/Italian/Portuguese/other), tobacco, diabetes, first 3 outcomes, vitals (blood pressure, heart rate, respiratory rate), and time data on the ABG procedure.

After the ABG procedure, the evaluator will fill in the third part of the paper CRF, containing the 5 outcomes, the level of overall satisfaction, the vitals (blood pressure, heart rate, respiratory rate), the number of arterial punctures observed on the skin, and the type of words used by the doctor during the procedure according to the patient.

The fourth part of the paper CRF certifies that the patient has received the complete information about the study, whether the patient has consented, and, if they have consented, whether they have received a copy of the signed informed consent form.

The fifth part of the paper CRF contains the following information extracted directly from the patient's file: age, sex, first and last names of the attending physician, duration of the ED visit (difference between admission and discharge from the ED, difference between admission to the ED and the patient's placement in the cubicle), reason for admission to the ED (Swiss emergency triage scale [U1-U4]), list of emergency reasons, BMI (weight/(height in m × height in m), and the patient outcome after the emergency stay (inpatient/outpatient/death).

The evaluator will confirm the accuracy of the data collected.

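### Covariate adjustment under a blanket no-imputation rule removes randomised patients who have both pain scores whenever a baseline covariate is blank

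*Protocol article*

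**What the plan says.** All of the following is in the protocol article.

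- **Model.** Under Statistical Analysis Plan, the three hypotheses are tested with linear mixed models on all available data. The effects of time, group and their interaction "will be tested by controlling for sociodemographic characteristics and variables linked to health status". No unadjusted model is given for pain.
- **Missing data.** The same section says "Statistical analysis will be performed on available data, and no imputation of missing data will be conducted". It makes no distinction between outcomes and baseline covariates. Few missing values are expected, for two reasons: one-to-one contact with a research team member, and previous experience.
- **Analysis set.** An intention-to-treat analysis is promised, alongside per-protocol and communication-based analyses.
- **Source of the covariates.** Under Case Report Form, education, native language, tobacco, diabetes and vitals are recorded by the assessor before the procedure. Other items come from the record: "The fifth part of the paper CRF contains the following information extracted directly from the" patient's file. These include age, sex, triage level, reason for admission and BMI.

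**The concern.** This point is not about missing pain scores. A likelihood-based mixed model handles an absent outcome row without imputation, so the rule is defensible for outcomes. It does something different to covariates. A patient-level covariate takes the same value on both of a patient's rows, so if it is blank both rows go, and with them two observed pain ratings. R and Stata, the named packages, drop such rows by default.

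Two things are at stake. The analysis called intention-to-treat would leave out randomised patients whose primary outcome is known. Power would also be lost for a reason that has nothing to do with outcome collection.

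The one-to-one interview does not protect against this for items read from the patient's file. BMI is an example, if it is used as a covariate: it needs both weight and height.

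**Working it through.** **Inputs** (Sample Size Calculation): "With a significance level of .05, a power of 0.9"; "a difference in pain on the VRS of 1.5"; "with an expected SD of 2.5"; "an attrition of 20"%; and the result, "we must include 83 patients in each group to show the efficacy of the intervention on pain by applying the Bonferroni correction". Neither the sidedness nor the number of comparisons is stated. The rates of blank covariates used below are assumptions.

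**Step 1: reproduce 83 per arm.** Take two comparisons (positive against neutral and against nocebo) and two-sided alpha .05/2 = .025.

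- n = 2 × (2.241 + 1.282)² × (2.5/1.5)² = 2 × 12.41 × 2.778 = 68.95, so 69.
- 69 × 1.2 = 82.8, so 83, which matches.
- A second route also gives 83: a t test at one-sided .05/3 needs 66, and 66/0.8 = 82.5.

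After 20% attrition, 83 × 0.8 = 66.4. That is below the 69 of the first route and only just meets the 66 of the second, so there is no reserve for further exclusions.

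**Step 2: confirm the row loss.** 249 patients at two time points give 498 rows. If one covariate is blank for 25 patients, 498 − 2 × 25 = 448 rows should remain. A mixed model fitted to simulated data of this shape, with BMI as the covariate and incomplete rows dropped, used 448 of 498 rows. All 25 patients were lost although their pain scores were present.

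**Step 3: power.** With a share p of patients having any blank covariate, n = 66 × (1 − p) per arm. Power is that of a two-sample t test with noncentrality 0.6 × √(n/2), where 0.6 = 1.5/2.5.

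| p (assumed) | n per arm | Power, two-sided .025 | Power, two-sided .05/3 |
|---|---|---|---|
| 0 | 66 | 0.879 | 0.845 |
| 5% | 62.7 | 0.861 | 0.823 |
| 10% | 59.4 | 0.840 | 0.798 |
| 20% | 52.8 | 0.789 | 0.741 |

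At .025 the cost is about 2, 4 and 9 percentage points. If there were no other attrition, starting from 83 per arm (0.945), the same shares would give 0.933, 0.918 and 0.881.

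**Step 4: how p could arise.** With k covariates each blank at rate m independently, p = 1 − (1 − m)^k.

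- Five covariates at 1%: p = 4.9%, power 0.861.
- Ten at 2%: p = 18.3%, power 0.799.
- Five at 5%: p = 22.6%, power 0.774.

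If blanks cluster in the same patients, p is smaller than this formula gives.

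**The case against.** The best defence is that the loss depends on a covariate list that the article does not give and may properly leave to the analysis plan. BMI is collected but nowhere named as a covariate. If the list is age, sex and triage level, there may be almost no blanks. The article expects few missing values and cites previous experience as well as one-to-one contact; the former is not confined to interview items. The 20% attrition is not limited to missing pain scores, so some covariate loss might fall within it, although exclusions after two failed punctures draw on it too. Nor does the text prescribe a complete-covariate analysis in so many words: a missing-category level is arguably not imputation at all.

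Most of this stands, and it limits the size of the problem. The absence of a covariate list is not the fault. What remains is the stated rule: it covers all missing data, sits beside mandatory adjustment, and gives a poor instruction whenever a covariate is blank. Previous experience is cited without a rate.

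Three stronger readings are tempting and are not supported.

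- **Bias.** A reader might infer that the arm comparison is biased because file completeness tracks acuity, and acuity tracks pain. Nothing in the article shows that link. Blanks in pre-procedure characteristics should not differ by randomised arm.
- **A very large loss.** Eight covariates each 5% blank and independent would remove 1 − 0.95⁸ = 34% of patients, leaving 44 per arm and power of 0.70. That stacks pessimistic assumptions, and no figure in the article points to it.
- **A different primary model.** One might want to replace the time-by-group model. That is a preference; the defect does not require it.

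**Conclusion.** The point holds as a modest, avoidable defect. Followed with default software behaviour, the combination of adjustment and no imputation excludes randomised patients with observed pain scores. The certain consequences, whenever a covariate is blank, are a departure from the intention-to-treat set and lost power; bias in the arm comparison does not follow from the exclusion alone.

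The size is unknown. Power of about 0.86, 0.84 or 0.79 (against 0.88) rests on assumed incompleteness of 5%, 10% or 20% on top of the full 20% attrition, on the two-comparison, two-sided reading of the Bonferroni correction, and on a plain t test that takes no credit for precision gained from covariates or baseline pain. If the covariates prove nearly complete, little is lost. The change is still worth making, because it costs almost nothing and the sample size has no reserve.

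**What to change.** Before analysis, amend the missing-data sentences under Statistical Analysis Plan as follows:

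- State that the no-imputation rule applies to outcomes only.
- Adjust only for covariates fixed before the procedure. The case report form also holds post-procedure vitals, length of the emergency stay and disposition, which should not be used.
- Fill blank baseline covariates by single imputation that ignores arm (such as the overall mean), or by a missing-category level for categorical items. Every randomised patient with a pain score then stays in the primary model. Simple methods of this kind are adequate for baseline covariates in a randomised comparison.
- Report the same model without these covariates as a sensitivity analysis.

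The time-by-group mixed model can stay as it is. The cost is one or two sentences and slightly more analysis work, with no extra patients or data.
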